## 1-Proof of research:

Osteoarthritis of the temporomandibular joint (TMJ) is a frequent cause of arthromyalgia of the face grouped under the acronym DAM (Dysfunction of the Manducator Apparatus). It can be expressed by a wide range of symptoms dominated by pain in the TMJs, associated or not with limitations in mouth opening, or even by blockages, joint noises and other signs such as bruxism, otalgia or tinnitus. These pains can be accompanied by functional disorders such as a limitation of the mouth opening, evaluated by the inter-incisor distance (IDI), sometimes linked to a dislocation of the disc (or meniscus) which is interposed between the condylar process of the mandible and the glenoid cavity of the temporal bone. The management of this pain is essentially based on empirical means, prescribed out of habit and without any real evaluation (analgesics, NSAIDs, muscle relaxants) as well as on the wearing of occlusal splints and/or occlusal equilibration by adding composite resins. In the event of failure of first-line treatments, the treatment is based on corticosteroid infiltrations, the effectiveness of which is transient, or on the injection of hyaluronic acid (HA) also called viscosupplementation.

1

A meta-analysis including 19 studies showed that in DAM in general (12 with disc problems and 7 with inflammatory flare-ups of degenerative arthropathy) (1) HA injections provide a greater reduction in pain than placebo (saline solution) in all cases where it was compared to it, and overall comparable to corticosteroid infiltrations. In another meta-analysis that included 18 studies on the use of HA in TMJ osteoarthritis, Escoda-Francolí et al (2) reached similar conclusions and proposed a "Strong" strength of recommendation regarding the indication of viscosupplementation in degenerative TMJ disorders (osteoarthritis and meniscopathy). Finally, the authors of the Cochrane review (3) conclude that HA injections provide a long-term improvement in the symptoms of TMJ osteoarthritis, that their beneficial effects are equivalent to those of glucocorticoids, and that one can optimize their results by combining them with arthrocentesis.

[figure not shown]

The objective of this research is therefore not to demonstrate the effectiveness of viscosupplementation in painful degenerative pathologies of TMJ **but to seek clinical factors predicting the success or failure of treatment** such as clinical severity before the injection, the presence of a limitation of the mouth opening or the duration of the symptoms.

For this we place ourselves **in the conditions of daily practice, in patients with symptomatic temporomandibular osteoarthritis with no other selection criteria** than the opinion of the investigator concerning the merits of viscosupplementation and the agreement of the patient participating in the research. **It in no way modifies the patient's therapeutic management and imposes no other constraint on him than filling in simple questionnaires commonly used in daily practice, in the monitoring of this pathology.**

## **2- Population concerned:**

Forty patients with temporomandibular osteoarthritis confirmed radiologically by a pantogram dating less than 12 months and justifying, in the opinion of the rheumatologist and/or the dental surgeon, viscosupplementation.

### **Inclusion criteria:**

Those in **daily clinical practice**, i.e. all ambulatory patients over 18 years of age, of both sexes, whose clinical diagnosis of temporomandibular osteoarthritis is confirmed by a dental panoramic radiograph less than 12 months old, and for which the indication for viscosupplementation has been selected by the medical specialist, rheumatologist or dental surgeon, on the basis of the usual clinical criteria (pain, discomfort when chewing, insufficient efficacy or poor tolerance of analgesics and/or anti-inflammatories).

### **Exclusion criteria:**

- Patients with a contraindication to viscosupplementation with HAppymini® hypersensitivity to hyaluronic acid or mannitol) or to

[figure not shown]

intra-articular injection procedure (current general infectious disease, infected skin lesions near the injection site, dental infection).

- Patients in whom the evaluation of the effectiveness of the treatment could not be carried out reliably:
  - Patients who received a viscosupplement in the target joint during the previous 6 months,
  - Patients who have received an intra-articular injection of corticosteroids in the target joint during the previous 3 months,
  - Patients undergoing planned surgery within 3 months of injection that may interfere with follow-up or evaluation,
  - Patients who do not speak French or who are unable to give their consent personally.

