##### 4-1. During the initial visit, the investigating doctor :

- gives the patient the information note, answers their questions and obtains their oral consent,
- verifies that the inclusion and exclusion criteria are respected,
- completes, in the data collection notebook assigned to the patient, according to the methodology developed in § 3-1,
- fills in the section "treatments for temporomandibular osteoarthritis", all treatments being authorized according to the rules of an observational study, provided they are collected,
- checks that the dental panoramic X-ray is less than 12 months old and asks for another one if necessary, as recommended before any intra-articular injection into the ATM.
- schedules or performs the intra-articular injection of HAppymini® hyaluronic acid himself. The injection may be performed the same day or for organizational reasons within a maximum period of 15 days, in order to limit the risk of variation in the clinical condition between the assessment and the date of the injection.

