##### 4-2. During the intermediate visit on D90 (+ or - 14 days) and the final visit on D180 the investigator:

- postpones to the end of the CRF any changes in concomitant treatments for TMJ osteoarthritis,

[figure not shown]

- reports any adverse events that have occurred since the day of the injection, and will specify whether or not they are attributable to the treatment or the procedure,
- completes the CRF according to the methodology developed in § 3-2.

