### 7- Duration of the study

This observational study requires a follow-up period of 6 months. The expected start date of recruitment is 01/04/2016. Recruitment will end when 44 patients have been included, in order to obtain 40 complete files, taking into account a percentage of trial dropouts and loss of follow-up of 10%. Recruitment time is estimated at 6 months. The total planned duration of the study is therefore 12 months.

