#### 8-2. The endpoint is the response to treatment.

The aim of the study being the search **for predictive factors of response to treatment**, it is not relevant to determine a primary endpoint. We will study the possible correlation between the response to the treatment and the level of pain on D0, the duration of the symptoms, the presence of a limitation of the mouth opening, and the existence of radiological lesions of osteoarthritis on the panoramic dental picture.

[figure not shown]

The response to the treatment will therefore be estimated by 3 complementary methods and for each of them the predictive factors of response (YES/NO) will be studied. Each patient will be classified into a treatment response category: YES or NO depending on:

1. The patient's assessment of the effectiveness (effective and very effective = YES, not or only slightly effective = NO),
2. Reduction in pain of at least 3 points or at least 50% on the Likert scale.
3. The degree of patient satisfaction (Very satisfied and fairly satisfied = YES, little or not satisfied = NO),

We will look for predictive factors of response or non-response, first in univariate analysis then in multivariate analysis by integrating all the factors with a  $P < 0.1$  in the univariate analysis, as well as possible confounding factors such as age, gender, taking NSAIDs, wearing a tray.

The main analysis will be carried out on the per-protocol population including only patients for whom all the data at D0 and D180 are available, then confirmed by ITT. For patients who do not have D180 data, the latest data available (D90) will be used (LOCF). The regression coefficients of the multivariate models (ANCOVA and mixed model) will be considered significant if the degrees of significance are less than 5%. Statistical analyzes will be performed with XLStat software.

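### The planned-surgery exclusion ends at 3 months but response is judged at D180, and the pain-reduction rule does not account for surgery or a further joint injection in between

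*Protocol*

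**What the plan says.** The protocol's exclusion criteria contain a group introduced as "Patients in whom the evaluation of the effectiveness of the treatment could not be carried out reliably". Three of its items concern other treatment:

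- earlier viscosupplementation of the same joint, with a look-back of 6 months;
- earlier corticosteroid infiltration of the same joint, with a look-back of 3 months;
- later surgery, worded as "Patients undergoing planned surgery within 3 months of injection that may interfere with follow-up or evaluation".

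The first two look back from the study injection. Only the third looks forward, and it stops at 3 months.

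Section 7 states: "This observational study requires a follow-up period of 6 months". Section 8-2 places the main analysis in a per-protocol population "including only patients for whom all the data at D0 and D180 are available". An ITT analysis follows, with D90 carried forward when D180 is missing.

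On other care, section 4-1 has "all treatments being authorized according to the rules of an observational study, provided they are collected", and section 4-2 has the investigator note "any changes in concomitant treatments for TMJ osteoarthritis" at D90 and D180.

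Section 8-2 classes each patient YES or NO in three ways: the patient's rating of effectiveness, a fall in pain of at least 3 points or at least 50%, and the patient's satisfaction. None of the three refers to the treatment record.

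**The concern.** The surgery criterion has a stated purpose, which is a reliable evaluation of the injection. The evaluation that carries the main analysis takes place 3 months after the criterion stops applying. Surgery known at enrolment to fall in month 4 or 5 is not excluded, although it can change pain and mouth opening before D180.

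The pain rule has a related gap. It compares two pain scores and takes no account of what happened between them. A patient whose pain falls by 3 points after surgery on the joint, or after a corticosteroid or second viscosupplement injection into it, is a responder to the study injection by this rule.

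The study seeks predictors of response, such as pain at D0 and symptom duration. If further treatment is more common at one end of a predictor, the resulting misclassification depends on that predictor and can weaken or distort the association. It would not be mere noise. That severe or long-standing cases are retreated more often is plausible, but the protocol does not say so.

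**Working it through.** **1. Exclusion window against evaluation time.** Inputs: surgery exclusion of 3 months (exclusion criteria), follow-up of 6 months (section 7), main analysis on D0 and D180 data (section 8-2).

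- Covered: about 90 of 180 days, 90/180 = 50%.
- Not covered before the main assessment: 180 − 90 = 90 days.

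The criterion protects the D90 visit. It does not protect D180.

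**2. Does anything later in the plan remove these patients?**

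- The per-protocol set is defined by data completeness alone. A patient operated on in month 4 who attends D180 is in it.
- Carrying D90 forward applies only when D180 is missing, so it does not replace a D180 value obtained after surgery.
- The adjustment factors are given as examples. The co-treatments named are NSAIDs and the tray, not surgery or a joint injection.

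**3. The protocol's own standard for joint injections.** Before the study injection, a corticosteroid within 3 months or a viscosupplement within 6 months in the target joint is enough to make the evaluation unreliable. Apply the same intervals backwards from D180:

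- a corticosteroid given between D90 and D180 lies within 3 months of the assessment;
- a second viscosupplement at any time after the study injection lies within 6 months of it.

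Neither has any consequence in the pain rule.

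**4. Size per patient.** The planned figure is 44 recruited for 40 complete files with 10% loss: 40 × 1.10 = 44, while 40/(1 − 0.10) = 44.4, which rounds up to 45. The difference does not matter here. I use 40 as the denominator.

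- One patient turned from NO to YES: 1/40 = 2.5 points.
- If 5%, 10% or 20% of patients were so treated (assumed): 2, 4 or 8 patients, and at most 5, 10 or 20 points.

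These are upper bounds. They require every such patient to be a true failure who then meets the pain rule because of the later treatment.

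**5. Illustration for the association.** All inputs are assumed: a predictor splitting the patients 20 and 20, true response 60% and 30%, two-sided 5%, normal approximation for two proportions, and later treatment turning a share q of non-responders to YES in the worse group only.

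Observed rate in the worse group = 0.30 + 0.70 × q. Odds ratio = (0.60/0.40) ÷ (observed rate/(1 − observed rate)).

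| q | Patients turned (of 14 non-responders) | Observed rate | Odds ratio | Power |
|---|---|---|---|---|
| 0 | 0 | 30% | 3.50 | 48% |
| 0.10 | 1.4 | 37% | 2.55 | 30% |
| 0.20 | 2.8 | 44% | 1.91 | 17% |
| 0.30 | 4.2 | 51% | 1.44 | 8% |

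About three such patients, all in one group, would nearly halve the odds ratio. If later treatment were spread over both groups the pattern would differ, and if it were concentrated in the better group it would inflate the association.

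**The case against.** The strongest reply is that this is a daily-practice study. Section 1 says that it does not change the patient's management, and section 4-1 deliberately leaves all treatment free. Analysing what is observed at D180, whatever was given in between, is a legitimate choice, and the detailed handling of later treatment often sits in a statistical analysis plan, which is not at hand. This stands as far as it goes. Free co-treatment is not an error, and the observed-value analysis should stay. It does not answer the window mismatch, where the protocol sets a criterion for a stated purpose and stops it halfway to the main assessment. Nor does it fully excuse the pain rule, because section 8-2 itself fixes both the response definitions and the analysis set.

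A reader might infer that all three definitions credit the injection after later treatment, and that such patients should be classed NO in all of them. The text does not support that. The effectiveness and satisfaction ratings ask about the treatment, so a patient who went on to surgery can answer that it was not effective. Nothing guarantees such an answer, but forcing NO would override the patient's own rating and would build the decision to retreat into the association under study. That is a trade-off, not a correction.

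The study is also exploratory, and the frequency of such events is unknown. This limits the weight of the point but does not remove it.

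**Conclusion.** The point holds in two parts. First, the 3-month surgery exclusion and the D180 evaluation do not fit together: half of the follow-up is uncovered, and affected patients remain in the main analysis set. This follows from the text alone. Second, the pain-reduction rule, and mainly that rule, counts improvement after target-joint surgery or a further injection as response, although the protocol has such treatment recorded.

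The size is bounded per patient, at 2.5 points in 40, but the total is unknown because the documents give no frequency of later surgery or injection. The odds-ratio illustration shows that a few patients can matter. It is not an estimate for this study.

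Two further inferences should not be drawn. One is that a true 50% response would be reported as 55–60%: this takes an assumed 2 to 4 converted patients (22/40 and 24/40 against 20/40) and is an upper bound. The other is that NSAID and tray use after the injection will enter the models. Section 8-2 gives no date for these factors, but it calls them possible confounders alongside age and gender, and section 3-1 collects both at D0.

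**What to change.** 1. **Exclusion criteria.** Reconcile the planned-surgery window with the D180 evaluation. If the sponsor keeps the present window, the protocol should say why and how patients with surgery before D180 are analysed. Which window is right is for the sponsor to decide.

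2. **Section 8-2.** Add, at least as a sensitivity analysis: *The pain-reduction response will also be analysed with patients who had recorded surgery on, or a further intra-articular injection into, the target TMJ before D180 counted as non-responders. The result will be reported beside the analysis of observed D180 values, with the number of such patients.* The effectiveness and satisfaction definitions stay as they are.

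**Cost.** The first change affects eligibility and may lose a few patients in a study that intends little selection. The second is analysis only. It needs no new visit or treatment rule, because section 4-2 already asks for treatment changes. The sponsor should check that the CRF entry gives the type, side and date of surgery or injection. The pain-reduction response rate in the added analysis may be slightly lower.

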### 3- Course of the study

Single-center study carried out within the framework of the multidisciplinary consultation for chronic stubborn pain at the Lannion-Trestel Hospital Center, 22660 Trévou-Tréguignec.

The recruitment of patients and their follow-up will be carried out by the dental surgeon specializing in occlusology, and/or the rheumatologist of the multidisciplinary consultation for oro-facial pain.

#### 3-1. During the selection visit (D0), the following elements will be collected:

- Demographics (gender, age, height, weight)
- Length of pain
- The target side

[figure not shown]

- Previous treatments for the pathology evaluated (NSAIDs, analgesics, muscle relaxants, infiltration of corticosteroids into the painful TMJ, injections of hyaluronic acid into the painful TMJ, specific rehabilitation of the oral sphere, wearing an occlusal splint)
- The search for bruxism, noises and / or crackles during chewing,
- TMJ pain on chewing measured on an 11-point numerical scale, "0" meaning "no pain" and "10" meaning "intolerable pain" (Likert 0-10),
- TMJ pain on palpation (Likert 0-10),
- The inter-incisor distance (IID) at the maximum opening of the mouth, measured in millimeters using a caliper.

**3-2. During the visits at 3 (D90) and 6 months after the injection (D180) the following elements will be collected:**

- TMJ pain when chewing (Likert 0-10),
- TMJ pain on palpation (Likert 0-10),
- IID at maximum mouth opening (mm)
- Patient satisfaction with the treatment (4-point Likert where 0 means "Not satisfied" and 3 means "Very satisfied")
- The patient's perception of the effectiveness of the treatment (4-point Likert where 0 means "Not effective" and 3 means "Very effective")
- The patient's perception of the reduction in pain in 6 categories: [0%]; [1-24%], [25-49%], [50-74%], [75%-99%], [100%]
- The change in his consumption of analgesics or anti-inflammatories compared to D0 ([YES/NO] and if [YES] quantification on a 5-point Likert scale ([1-24%], [25-49%], [50-74%], [75%-99%], [100%]))
- Any adverse effects during the D90 visit (to ensure quality monitoring of the treatment)

[figure not shown]

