### **10-1 Collection of adverse events by the investigators**

- Collection of non-serious adverse events: Investigators must note all adverse events, even non-serious, on the adverse event form in the observation notebook.
- Reporting of serious adverse events: In the event of a serious adverse event, the investigator has the obligation to report it without delay to the

[figure not shown]

promoter who immediately sends it to the distributor (Laboratoire Labrha) who himself informs the manufacturer of the medical device within 24 hours (Laboratoire Vivacy, Archamps, France), according to the internal procedures of the 2 companies:

- on a specific form attached to the observation book: "Serious Adverse Event Declaration Form",
- form to be sent by email within 24 hours after learning of the event, to the Proponent's Materiovigilance Manager at the following address: [[contact]](mailto:[contact])

12

If this is not possible, the information must be communicated by telephone within the same timeframe to the Vigilance Manager on [name].

The causal link with the medical device and/or its administration procedure must be suggested by the investigator (none, possible, probable, proven).

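### Section 3-2 records a change in analgesic or anti-inflammatory use without its direction, and lists adverse effects at D90 only, against sections 4-2 and 10-1

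*Protocol*

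**What the plan says.** Section 3-2 lists eight items to be collected at D90 and D180. Two matter here.

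- **Drug use.** The item is "The change in his consumption of analgesics or anti-inflammatories compared to D0 ([YES/NO] and if [YES] quantification on a 5-point Likert scale". The five classes are 1-24%, 25-49%, 50-74%, 75-99% and 100%.
- **Adverse effects.** Under a heading that covers both visits, the entry reads "Any adverse effects during the D90 visit (to ensure quality monitoring of the treatment".

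Section 4-2 covers the same two visits: "During the intermediate visit on D90 (+ or - 14 days) and the final visit on D180 the investigator" "reports any adverse events that have occurred since the day of the injection". It also has changes in concomitant treatment for the joint disease noted at the end of the CRF. Its last instruction is that the investigator "completes the CRF according to the methodology developed in § 3-2". Section 10-1 sets no time limit: "Investigators must note all adverse events, even non-serious, on the adverse event form in the observation notebook".

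Section 8-2 defines response (YES/NO) in three ways: the patient's rating of effectiveness, a fall in pain of at least 3 points or at least 50% on the Likert scale, and satisfaction. It names NSAID use among the possible confounders for the multivariate models.

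**The concern.** The study looks for factors that predict success or failure of the injection. Section 4-1 allows every other treatment provided it is recorded, and insufficient effect or poor tolerance of analgesics or anti-inflammatories is among the usual reasons for entry in section 2. Drug use may therefore move in either direction during follow-up. A fall in pain with less medication means something different from the same fall with more. The item in section 3-2 is the only one that quantifies this movement, and as worded it leaves out the sign. An analysis plan cannot supply a sign that was never collected.

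The adverse-effect entry raises a different problem. Sections 3-2 and 4-2 disagree on whether the D180 visit collects adverse events, and the section with the wider rule defers to the narrower one for the content of the CRF.

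**Working it through.** The protocol gives no figure to reproduce. The check is whether each response scale can hold the values that may occur, and whether the sections agree.

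**1. Drug-use item.** Change = (use at follow-up − use at D0) / use at D0. The doses per week below are assumptions for illustration only.

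| D0 → follow-up | Change | Read literally as change | Read as reduction |
|---|---|---|---|
| 4 → 0 | (0−4)/4 = −100% | YES, 100% | YES, 100% |
| 4 → 2 | (2−4)/4 = −50% | YES, 50-74% | YES, 50-74% |
| 4 → 4 | 0% | NO | NO |
| 4 → 6 | (6−4)/4 = +50% | YES, 50-74% | NO |
| 4 → 8 | (8−4)/4 = +100% | YES, 100% | NO |
| 4 → 10 | (10−4)/4 = +150% | YES, no class fits | NO |

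On the literal reading, +50% and −50% share a code, as do doubling and stopping, and +150% has no class. On the reduction reading, every increase is merged with no change. Neither reading identifies an increase.

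**2. Can other records supply the sign?** Section 3-1 lists previous treatments by type, without amounts. Section 4-1 has a CRF section for treatments of the joint disease, and section 4-2 has changes to them noted at both visits. Neither states that a dose or frequency must be entered. A drug started or stopped should appear there; a change in the amount of a drug already taken appears only if the investigator writes it down.

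**3. Does the item enter the response classification?** No. None of the three definitions in section 8-2 names it.

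**4. Can the other items in section 3-2 show worsening?** Chewing pain (0-10), palpation pain (0-10) and inter-incisor distance (mm) are measured at D0, D90 and D180. With illustrative values, chewing pain from 5 to 8 is +3 points and opening from 35 to 30 mm is −5 mm. So 3 of the 8 items record deterioration directly. The perceived-reduction item does not: "The patient's perception of the reduction in pain in 6 categories: [0%]; [1-24%], [25-49%], [50-74%], [75%-99%], [100"%] starts at zero, so a patient who is worse and one who is unchanged share a class.

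**5. Adverse events, side by side.**

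| Section | Visits or period | Scope |
|---|---|---|
| 3-2 | D90 visit only | any adverse effects |
| 4-2 | D90 and D180 | all events since injection; CRF completed as in 3-2 |
| 10-1 | no limit stated | all events, on the adverse event form |

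If the D90 visit falls on day 90, the section 3-2 list has no adverse-effect entry for the following 180 − 90 = 90 days, half of follow-up. With the ±14 days of section 4-2, the D90 visit falls between day 76 and day 104, so the uncovered part is 76 to 104 days (76/180 = 42% to 104/180 = 58%), taking the final visit on day 180.

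**The case against.** There is a good case that this is minor.

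- **The reduction reading is plausible.** The five classes match those of the perceived pain reduction item directly above. On that reading reductions are coded correctly. This stands, but it only moves the problem: increases then look like no change.
- **The CRF is not shown** and may already ask for a direction. This stands as a limit on certainty; the protocol text does not require one.
- **There is a second record, and queries are possible before the database is frozen.** A reader might infer that the missing sign can never be recovered. The documents do not support that: section 4-2 may supply it for some patients. They do not ensure it for all, because no quantity is required.
- **Responders might seem to be misclassified.** They are not, since no response definition uses the item. Even if the 50% rule were applied to the perceived-reduction classes, worse and 0% would both be NO.
- **NSAID use as a confounder may mean use at D0.** Section 8-2 does not say at which time it is taken. If only D0 use is meant, the adjustment is unaffected and the loss is confined to interpreting the pain response.
- **Adverse events have their own form.** A reader might infer that events after D90 will be lost. Sections 4-2 and 10-1 both require them, so the documents show a contradiction that creates a risk of loss, not a loss.

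**Conclusion.** The point holds in a limited form. As written, the drug-use item cannot identify an increase on either reading and has no class above 100%. The concomitant-treatment record is a partial back-up. The effect falls on interpretation of the pain response and, if follow-up use is meant, on NSAID use as a confounder. The YES/NO response classifications are unchanged.

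Its size cannot be stated. The protocol does not say how many patients are expected to raise or lower their use, and any percentage would rest on invented counts. Each patient who raises it is 1/40 = 2.5% of the planned complete files.

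The adverse-event contradiction between section 3-2 and sections 4-2 and 10-1 is certain from the text. It concerns about half of follow-up if a CRF is built on the section 3-2 list alone.

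A reader might go further and infer that the follow-up items cannot record deterioration at all. That is not supported: both 0-10 pain scales and inter-incisor distance show worsening against D0. For the same reason the zero floor of the perceived-reduction item is not a defect that needs correction. The conclusion assumes that the CRF follows the protocol wording.

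**What to change.** 1. In section 3-2, replace the YES/NO part of the drug-use item with decreased / unchanged / increased, followed by the percentage class, and add a class above 100% for increases.
2. Reconcile the adverse-effect entry in section 3-2 with sections 4-2 and 10-1, so that the CRF collects adverse events at both D90 and D180.
3. Optional: add a *worse* class to the perceived pain reduction item. It would change no response result, and the two 0-10 scales already capture worsening.

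The cost is two wording changes to the protocol and CRF (three with the optional one), with no extra visit, staff or procedure. The change to the drug-use item has to be in place before data are collected, because a direction left out at a visit may not be recoverable later.
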